### Study treatment

Participants are randomized 1:1:1 to one of three CS1 dose levels, with a target of 10 participants per dose level: 480 mg/day (1 × 160 mg capsule in the morning and 2 × 160 mg capsules in the evening); 960 mg/day (1 × 160 mg capsule in the morning and 2 × 160 mg capsules in the evening for 3 days; if tolerated this is followed by 2 × 160 mg capsules in the morning and 4 × 160 mg capsules in the evening for the remainder of the study); 1920 mg/day (1 × 160 mg capsule in the morning and 2 × 160 mg capsules in the evening for 3 days; if tolerated this is followed by 2 × 160 mg capsules in the morning and 4 × 160 mg capsules in the evening for 7 days; if tolerated this is increased on Day 11 to 4 × 160 mg capsules in the morning and 8 × 160 mg capsules in the evening for the remainder of the study). If the dose of CS1 following an increase is not tolerated, the dose is reduced. If the participant cannot tolerate the reduced dose they are withdrawn from the study but continue to be evaluated. No dose escalation is planned as the effect of CS1 on outcome measures other than safety and tolerability will not be evident until the study has concluded, and all participants are already receiving standard of care therapy. CS1 is formulated as controlled‐release capsules with mini‐tablets designed to release the active substance with a peak 10 h after administration containing in total 160 mg sodium valproate, which was manufactured by Galenica AB, for further details see the Phase 1 study publication.^46^ Participant number assignment and randomization will be conducted via use of an interactive response technology system at the screening and randomization visits.

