No placebo group was deemed necessary for assessment of safety and tolerability as VPA has a well‐known safety and tolerability profile from previous studies. The FDA had no requirement for a placebo group for a conclusive study and advised that the study had an adequate design both at pre‐investigational new drug (IND) discussions and when the final IND was submitted. The placebo effect for subjective endpoints, for example, 6MWD are well‐known from many PAH studies in similar populations. Most of the key secondary endpoints from CardioMEMS, RHC, pulmonary vascular resistance (PVR), echocardiography, cardiac magnetic resonance imaging (MRI), and biomarkers, and so forth are unlikely to have placebo effects. The recent PULSAR study with sotatercept showed a minimal and nonsignificant placebo effect with PVR as measured using RHC.^49^

Dose selection was based on animal studies in established models for the treatment and prevention of PAH.^35^, ^39^ The effective doses of VPA in these studies was equivalent to a human dose of 1120–3430 mg/day, which was calculated using the published guidance from the FDA.^50^ Therefore, the current study evaluates a dose in the lower range (480 mg/day) which was well tolerated in the Phase 1 study in which CS1, at a dose of 552 mg/day, reduced PAI‐1 significantly,^46^ and was the dose closest to the lowest effective dose in animals (960 mg/day) and a dose in the higher dose range (1920 mg/day). The two higher doses evaluated are higher than those administered in the Phase 1 healthy volunteer study to allow further evaluation of the dose response in PA pressure reduction, vascular remodeling, anti‐inflammatory, anti‐fibrotic, and anti‐thrombotic effects. VPA has been used in the treatment of epilepsy for many years at higher doses than those evaluated in the Phase 1 study, so determination of the maximum tolerated dose/dose‐limiting toxicities were deemed unnecessary. CS1 is administered in unevenly divided daily doses with the larger portion given in the evening to minimize the risk of AEs and maximize the effect on endogenous PAI‐1 levels, which are higher in the early morning hours.^42^

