### Sample size calculation

The main purpose of the study is to evaluate safety/tolerability of three different doses of CS1. In addition, exploratory evaluations of many relevant measurements for patients with PAH (see previous text sections) will be performed. For sample size calculation for the study, the estimate was based on the potential effect of CS1 on mPAP, with analysis according to multiple readings that increase the precision of PA pressure determination. A sample size of 10 subjects per dose level group has an 80% power to detect a difference in means of 15%, assuming that the common standard deviation is 5, with a 5% significance level.

PA pressure (mPAP) AUC will be the first secondary endpoint that will be tested statistically since the power of the study is based on that variable.

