### Statistical analysis

The study protocol and Statistical Analysis Plan will be published as appendices to the primary publication following the end of the study.

The Safety Analysis Set includes all randomly assigned participants who receive at least one dose of study drug and participants will be analyzed as treated. The PK Analysis Set will include all participants in the Safety Analysis Set who have at least one evaluable post‐baseline PK sample, and this will be used for all PK analyses.

All data listings, summaries, figures, and statistical analyses will be generated using SAS version 9.4. Summaries will be presented by dosing cohort and overall. The exploratory efficacy endpoints will summarized descriptively and analyzed using both intention to treat as well as per protocol approaches. Of the exploratory efficacy endpoints, mPAP which the study is powered for, will be tested first to detect mean differences among dosing groups. Descriptive statistics for categorical variables will include the number and percentage of participants with each characteristic. Percentages will be based on the number of participants with non‐missing values. Descriptive statistics for ordinal and continuous variables will include the number of participants, mean, median, standard deviation, minimum value, maximum value.

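### The 80% power is stated for one difference called the effect of CS1 on mPAP, and is not established for the planned test among three active doses

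*Protocol article*

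**What the plan says.** Sample size calculation: "the estimate was based on the potential effect of CS1 on mPAP". The section continues: "A sample size of 10 subjects per dose level group has an 80% power to detect a difference in means of 15" per cent, "assuming that the common standard deviation is 5, with a 5% significance level". It does not say which means are compared, what the 15% is a percentage of, the unit of the SD, or whether the test is one- or two-sided. It names the AUC of mPAP as the first secondary endpoint to be tested.

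Statistical analysis: of the exploratory efficacy endpoints, "mPAP which the study is powered for, will be tested first to detect mean differences among dosing groups". These endpoints are to be "analyzed using both intention to treat as well as per protocol approaches".

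Study treatment: "Participants are randomized 1:1:1 to one of three CS1 dose levels, with a target of 10 participants per dose level". The doses are 480, 960 and 1920 mg/day. On the control: "No placebo group was deemed necessary for assessment of safety and tolerability". The same section gives further evaluation of the dose response as a reason for including the two higher doses.

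Table 2 lists the CardioMEMS pressures as change from baseline to end of treatment, compared between CS1 doses.

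**The concern.** The article attaches a power figure to a test for which it was not evidently calculated. The effect of CS1 is a contrast between CS1 and no CS1. The test looks for differences among three groups that all receive CS1. The two coincide only if the lowest dose does nothing.

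Two things follow. First, a reader will take 80% as the chance that the between-dose test succeeds if CS1 works as hoped, and that chance may be far lower. Second, the test cannot answer the question behind the sizing. If every dose lowers mPAP by the same amount, a valid between-dose test rejects only at its 5% error rate. A flat result would then look the same whether all doses work or none does. The article says the data will inform Phase 3 planning, so misreading a flat result as no effect, or within-arm falls as efficacy, would carry forward.

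**Working it through.** **Inputs from the article.** Ten per group, three groups, 80% power, 15% difference, SD 5, 5% level. **Assumptions.** Two-sided tests, no dropout, equal variances.

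**Step 1: reproduce the 80%.** If 15 and 5 are on the same scale, the standardised difference is 15/5 = 3. A two-sample t-test with 10 per group then has more than 99.9% power, so 80% does not follow. Read the other way, 80% power in a two-sample t-test (18 df, noncentrality d·√(10/2)) needs d = 1.325 SD. With an SD of 5 mmHg that is 1.325 × 5 = 6.62 mmHg. This is 15% of 6.62/0.15 = about 44 mmHg. The article gives no mean baseline mPAP, only the entry floor of 25 mmHg. Over an assumed range of baselines, two-sample power is:

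| Baseline mPAP (mmHg) | 15% of it (mmHg) | Power |
|---|---|---|
| 25 | 3.75 | 36% |
| 40 | 6.00 | 72% |
| 45 | 6.75 | 81% |
| 60 | 9.00 | 97% |

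A within-group t-test would give 80% at a baseline near 33 mmHg. The two-sample basis is therefore an inference. The steps below take D = 1.325 SD from it.

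**Step 2: power of between-dose tests at 10 per group.** For the omnibus F test (2 and 27 df) the noncentrality is λ = 10·Σ(mᵢ − m̄)², with the dose means mᵢ in SD units. For a linear contrast in log dose (the doses double, so the scores are −1, 0, 1; 27 df) it is (m₃ − m₁)·√10/√2. Means are shown as multiples of D for 480, 960 and 1920 mg/day.

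| Pattern of means | λ | F test | Log-dose trend |
|---|---|---|---|
| *D is the low-to-high gap* | | | |
| 0, ½, 1 | 8.78 | 71% | 81.5% |
| 0, 0, 1 or 0, 1, 1 | 11.70 | 83% | 81.5% |
| *D is the top-dose effect against no CS1* | | | |
| ¼, ½, 1 | 5.12 | 47% | 57% |
| ⅓, ⅔, 1 | 3.90 | 37% | 48% |
| ½, ¾, 1 | 2.19 | 22% | 30% |
| 1, 1, 1 | 0 | 5% | 5% |
| *Only the middle dose works* | | | |
| 0, 1, 0 | 11.70 | 83% | 5% |

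Example for the first row: the deviations from the mean are −D/2, 0 and D/2, so λ = 10 × 2 × (1.325/2)² = 8.78.

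**Step 3: pairwise tests.** Top against low dose at 0.05/3, with D as the low-to-high gap, has 63% power in a two-sample t-test (66% with the error pooled over three groups). Three unadjusted pairwise tests keep about 80% for that pair, but their familywise error is about 12% by simulation.

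**Step 4: baseline adjustment.** The article gives no correlation between baseline and follow-up. Take the first row's trend contrast (81.5% unadjusted). If SD 5 is the SD of mPAP itself and the comparator is an unadjusted analysis of follow-up values, the residual SD is multiplied by √(1 − ρ²). Power is then 85%, 91% and 98% at ρ = 0.3, 0.5 and 0.7. If SD 5 is already the SD of the change, the variance factor is (1 + ρ)/2 and power is 94%, 91% and 87%. The gain runs in opposite directions with ρ, so it can only be shown as a range.

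**The case against.** The strongest reply has three parts.

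*The test fits a stated aim, and the endpoint is not primary.* Safety and tolerability are primary, mPAP is called exploratory, and the choice to have no placebo is explained openly. This stands. It limits the consequence, and the lack of a placebo is not itself the error. It does not remove the mismatch, because the article itself says the study is powered for the between-dose test.

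*The test, covariates, leading analysis set and multiplicity rule belong in the SAP.* This also stands. The article names no test, so the figures above describe candidate procedures rather than adopted ones. Using both intention-to-treat and per-protocol sets for exploratory endpoints is no fault. What remains is a conflict between two statements in the article.

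*The loss is not certain.* Correct. A reader might infer that either power is below 80% or the error rate exceeds 5%. The documents do not support that: the F test has 83% if the middle dose equals either end, and pairwise tests carried out only after a significant F test hold the familywise error at 5% with three groups.

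A reader might also infer that a single dose-trend contrast would restore the 80%. It does so only if the 15% is the low-to-high gap. If the 15% is the effect of CS1, as the sample size section words it, the trend has 30–57% in the graded patterns and 5% if the doses are equally effective. Against a response confined to the middle dose it has no power beyond the 5% error rate, where the F test has 83%.

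**Conclusion.** The point holds in a limited form. The sample size section and the analysis section describe different quantities, and the 80% is not established for the test to which the article attaches it. The shortfall is conditional. An omnibus F test has about 71–83% if 1.325 SD is the gap between lowest and highest dose, and about 22–47% if it is a graded top-dose effect against no CS1. If all doses work equally, power is 5%. These figures rest on an inferred two-sample basis, two-sided 5% tests, no dropout and the assumed response shapes.

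The 80% itself cannot be verified, because a relative 15% and an SD without a unit meet only through an unstated baseline mPAP, near 44 mmHg for a two-sample test with an SD of 5 mmHg. The article does not support a claim that the study is definitely underpowered, or that one particular test repairs it. Since mPAP is exploratory, this is something the sponsor should correct rather than a flaw in the primary objective.

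**What to change.** 1. State which means are expected to differ by 15%, the baseline mPAP to which the 15% refers, and the unit of the SD, including whether it is the SD of mPAP, of its AUC or of the change. Then restate the power for the between-dose comparison actually tested, or drop the power claim and report between-dose estimates with confidence intervals.
2. Include baseline mPAP, already collected during the baseline period, as a covariate in that comparison. Show any gain in power as a range over assumed correlations.
3. State that the test supports a dose-response conclusion only, that a flat result cannot separate equal efficacy from no efficacy, and that within-arm change is not controlled evidence of a CS1 effect.

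A single log-dose trend contrast is a reasonable option for the stated dose-response aim. With an evenly spaced response over the full gap it has 81.5% against 71% for the F test. If adopted, its weakness against a response peaking at the middle dose should be stated, and it should not be presented as restoring the 80%.

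The cost is wording and one recalculation, with no added patients or visits. The change should be made before data are compared by dose.

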## DISCUSSION

PAH remains a serious condition with great unmet need due to its incurable nature and significant associated morbidity and mortality. Currently approved therapies do not fully modify disease pathology and new treatments are therefore needed.

VPA has a multitude of effects that are amenable to treatment of PAH, including reverse remodeling of the underlying vascular changes, reduction of PA pressure, fibrosis, inflammation and thrombosis.^35^, ^36^, ^38^, ^39^ Sotatercept, which acts to reverse remodeling and reduce inflammation,^52^, ^53^ is efficacious in patients with PAH.^54^ Additionally, a meta‐analysis has shown that anticoagulation is associated with improved survival in patients with idiopathic PAH.^55^ CS1 therefore represents a novel approach to the management of PAH with a disease‐modifying potential.

Design of clinical trials is important to fully understand the mechanisms and benefits of new treatments. 6MWD has long been a fundamental outcome measure in studies investigating the effects of treatment in patients with PAH. However, a statistically significant change in 6MWD is not always clinically meaningful.^56^ More recently, composite endpoints encompassing both morbidity and mortality have been employed in clinical trials.^57^, ^58^ Time to clinical worsening (TTCW) is now a more widely used measure; however, there is no universal definition of TTCW, which makes comparisons between different clinical trials challenging.^17^ The use of composite endpoints also poses a further question regarding weighting of the individual components according to clinical importance and the frequency at which they occur.^59^ Further research is required to fully establish TTCW as a validated surrogate outcome for mortality in trials evaluating treatments.

Numerous potential pharmacological treatments for PAH have shown promise in preclinical models but have failed to show clinical benefit in humans or were associated with poor tolerability.^59^ There is an inherent issue with the use of preclinical models in that they do not closely approximate the disease in humans and typically do not involve background therapy, which is common in PAH patients. Furthermore, there is an unknown factor for potential off‐target effects of novel therapies. Refinement of preclinical testing is therefore needed to reduce false‐positive outcomes.

It has been suggested that the focus of early‐phase clinical trials in patients with PAH should be safety, determination of predictive biomarkers and identification of responders to treatment, while later‐phase trials should assess dose–response relationships and characterization of these responsive individuals.^59^ In the CS1 Phase 2 study, a wide array of functional, hemodynamic, and structural biomarkers as well as patient‐reported outcomes are being measured to provide an insight into not only treatment effects but the disease process itself. The use of highly discriminatory and calibrated risk stratification tools such as REVEAL 2.0 and REVEAL Lite 2 may also aid recruitment of a more homogeneous study population that may truly benefit from target drug application, i.e., enrichment. It has been shown that PAH patients who maintain a low‐risk status after initial treatment fare better than those who fall into the intermediate‐ and high‐risk categories^14^, ^60^, ^61^ and this also represents a valuable assessment of clinical worsening or improvement. In the FREEDOM‐EV study, a 1‐point decrease from baseline at Week 12 in REVEAL 2.0 score predicted a 62% reduction in the relative risk of clinical worsening, while a 1‐point decrease in REVEAL Lite 2 score predicted a 59% reduction in the relative risk of clinical worsening.^62^ The use of patient‐reported outcome measures (such as the Pulmonary Arterial Hypertension‐Symptoms and Impact Questionnaire and Minnesota Living with Heart Failure® Questionnaire included in the current study) also provide an insight into treatment effects distinct from those that are purely clinical or mechanistic.

Understanding hemodynamics at baseline and changes over time is also crucial to guide clinical management of patients with PAH. Notably, the recent Phase 2 clinical trial of sotatercept in PAH employed PVR as its primary endpoint, which was significantly different when comparing active treatment to placebo.^49^ It has been shown that the CardioMEMS HF System permits timely and consistent PA pressure monitoring that is associated with a more frequent medication changes and reduced hospitalizations in patients with heart failure regardless of left ventricular ejection fraction.^26^, ^31^, ^32^, ^34^, ^63^, ^64^, ^65^ Ambulatory PA pressure monitoring using CardioMEMS provides very frequent hemodynamic assessment in the patients’ normal environment, which more accurately assesses medication impact over time. Intermittent RHCs provide limited “real‐time” information about medication changes given the time between tests. This approach allows medication intervention studies to provide clearer data with fewer participants enrolled. Its use in the current study will provide greater insight into the real‐time evolution and stability/consistency of effects of CS1 at the level of pulmonary hemodynamics, PA and RV interactions, as well as provide important safety data using CardioMEMS in patients with PAH.

It is well‐established that the use of cardiac MRI is a valuable predictive tool for clinical worsening and mortality in PAH, in terms of tracking deterioration in RV function.^66^, ^67^, ^68^ In this study, the extensive imaging data captured will allow a precise insight into the adaptive change in RV response to therapy, which has been shown previously in a study of macitentan.^69^

In conclusion, CS1 represents a potential novel disease‐modifying treatment for PAH. The Phase 2 study described here will provide vital information regarding the safety of CS1 at three dose levels but will also include a broad range of endpoints encompassing clinical, hemodynamic, and PK parameters as well as patient‐reported outcomes. Topline results from this study are expected in the first quarter of 2024 and a quality analysis will be reported in the fall of 2023.

## ETHICS STATEMENT

The study is conducted in accordance with the ethical principles of the Declaration of Helsinki and International Conference on Harmonization Good Clinical Practice guidelines. The study protocol (version 3.0; December 9, 2022) was approved by the ethics committees at all participating study sites.
